##### Analysis of efficacy on primary and secondary outcomes

All statistical tests will be two-tailed and a *p* value < .05 will indicate statistical significance. Effect sizes will also be assessed. Standard descriptive statistics will be provided with means and standard deviation for demographics and baseline characteristics. Group comparisons will be made using t-tests for continuous variables and chi-square analyses for discrete variables.

The primary efficacy analysis will be done with a modified intention-to treat (mITT) approach. All participants will be included in the analyses and the characteristics of those who withdrew will be analysed, as well as the causes leading them to leave the study. A linear mixed model will be used to analyse the data, as it handles correlated data and unbalanced designs and are robust against missing values. The fixed effects will be Intervention (StayFitLonger vs. active control), Time (T0, T1) and their interaction. If the StayFitLonger training is more beneficial than the active control training, a significant interaction will be expected. In such case, the presence of a significant difference between T0 and T1 in each group will be evaluated, as well as group difference on change scores at post-training using the pre-training and control group as reference points. The same analysis will be used with primary and secondary outcomes. To examine the effect of frailty status on efficacy, participants will be stratified into robust and pre-frail seniors and data will be analyzed separately in these two populations using the same method described above.

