#### Study population

One hundred and twenty-eight French-speaking healthy participants will be recruited, 64 in Switzerland, 32 in Canada and 32 in Belgium. Participants will be community-dwelling older adults. They will be recruited through diverse sources including ads, newsletters, social media, and flyer distribution during various events. Recruitment will be carried out with the help of two community associations, Pro Senectute in Switzerland and Brusano in Belgium, and from the bank of participants of the IUGM research centre in Canada.

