#### Randomisation and blinding procedure

A randomisation list will be generated in Switzerland, independently from the research project and implemented using REDCap. In each site, a team member not involved in assessment or monitoring will assign participants by pressing a “randomisation” button on REDCap. A stratification will be done according to the frailty status. Within each stratum (robust and pre-frail), participants will be assigned to one of the two conditions (StayFitLonger or active control) according to separate randomisation schedules with a 1:1 ratio. Couples (e.g., married individuals) who participate in the study will be assigned to one of the two conditions as a pair: the first member of the couple will be randomised, and the second will be assigned to the same intervention. This has been implemented to avoid contamination in cases where two individuals living in the same household would be randomized to different training programmes.

Assessors will be blind to the hypotheses and to participants’ assignment, as they will only have access to the testing sessions. Participants will be asked not to discuss their training programme with assessors. If such a circumstance were to occur, it will be reported but should have minimal effect on data integrity, as assessors will be blinded to the hypotheses. Research team members responsible for the statistical analyses will be blind to the training conditions. Study coordinators and instructors involved in the introductory courses and supervision of home-based training will not be blind. Participants will be aware that the trial has two different training conditions and that they will be randomly allocated to one of them. However, they will not be informed of the study hypotheses and therefore will not know which one is the experimental condition. Both programmes will have a similar main screen layout and name, and the wording of the recruitment documents and consent forms will not convey the notion that one condition is hypothesised as inferior in terms of its effects on physical capacities and cognition [48].

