#### Statistical analyses

##### Sample size calculation

Given that our secondary analyses will stratify participants into two categories (robust and pre-frail), we determined our sample size to ensure that we have the capacity to test the hypotheses related to this stratification. This was done with a Marker Stratified Design using the following plan: marker-by-treatment interaction using separate test (see: http://www.bigted.org/NonAdaptiveDesigns/MarkerStratifiedDesigns.html). For pre-frail participants, it was estimated that 16 participants per group (StayFitLonger vs. active control) would be required to detect a significant difference of 3.22 s in the TUG test using a two-sided t-test (alpha = 0.05) based on the T&E pilot study. As data might not be normally distributed, a non-parametric test was required resulting in a sample size of about 18 participants per group. Considering a dropout rate of about 25% based on prior studies, a sample size of 24.5 pre-frail participants should be enrolled for each group. For robust older adults, a sample size of 23.5 participants per group would allow to detect a difference of 0.82 s on the TUG test using a two-sided t-test (alpha = 0.05) with a power of 80% based on the study by Uemura et al. [77]. By accounting for the non-normality of data (using a non-parametric test) and the dropout rate, we targeted recruiting 36 robust participants per group. Thus, a total sample of 122 participants was determined as sufficient to have the appropriate power based on sample size calculation. To have a balanced distribution in the three countries, the total N targeted for recruitment was set at 128 participants.

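### The primary mixed model leaves the baseline means free and omits the frailty stratifier, so it is close to an unadjusted change-score test: valid, but less efficient than a baseline-adjusted analysis

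*Protocol article*

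**What the plan says.** In the protocol article, under Analysis of efficacy on primary and secondary outcomes, the method is "A linear mixed model will be used to analyse the data", and its terms are listed: "The fixed effects will be Intervention (StayFitLonger vs. active control), Time (T0, T1) and their interaction". Efficacy is judged on the interaction. If it is significant, the plan goes on to changes within each arm, "as well as group difference on change scores at post-training using the pre-training and control group as reference points". The same analysis serves the primary and secondary outcomes.

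Under Randomisation and blinding procedure: "A stratification will be done according to the frailty status", with "separate randomisation schedules with a 1:1 ratio" inside each stratum. Site is not named as a stratifier. Frailty returns in the efficacy analysis only as a split of the sample: "data will be analyzed separately in these two populations using the same method described above".

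**The concern.** Randomisation makes the expected T0 means of the two arms equal, and TUG at T0 is measured on everyone. A model with a free Intervention main effect does not use that knowledge: it estimates a T0 difference known to be zero in expectation and subtracts it, with its sampling error, from the T1 difference. The factor that governs allocation is also missing from the model that draws the main conclusion.

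What is at stake is precision. The confidence interval for the primary comparison, and for every continuous secondary outcome analysed the same way, is wider than these data require.

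**Working it through.** **Inputs.** From the documents: the fixed effects; two time points; two-sided alpha 0.05; 25% dropout; 16 pre-frail per group for 3.22 s and 23.5 robust per group for 0.82 s, at 80% power (stated for the robust stratum only); total 122, target 128. Not in the documents, hence assumed: rho from 0.5 to 0.9, equal TUG variance at T0 and T1, 80% power for the pre-frail stratum, and a non-parametric inflation factor of 1.15.

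**1. The plan's own figure.** Pre-frail: 16 × 1.15 = 18.4, and 18.4/0.75 = 24.5. Robust: 23.5 × 1.15 = 27.0, and 27.0/0.75 = 36.0. Total 2 × 25 + 2 × 36 = 122, as stated. Solving the t-test power equation for the SDs gives about 3.15 s (pre-frail) and 0.98 s (robust).

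**2. What the interaction estimates.** With complete data it is (T1 − T0 in the experimental arm) minus (T1 − T0 in the control arm). In one complete simulated data set the stated model gave −0.1273 (SE 0.2248), and the plain difference in mean change gave the same. Adding frailty and site as main effects only left both numbers unchanged, because a term not crossed with Time does not touch the change.

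**3. Variance.** For a common variance s², up to the same factor in n:
- change score: 2s²(1 − rho)
- baseline-adjusted: s²(1 − rho²)
- ratio: (1 − rho²) / [2(1 − rho)] = (1 + rho)/2

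Effective sample gain is 1/ratio − 1. A test with 80% power as written would have power Φ[(1.960 + 0.842)/√ratio − 1.960].

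| rho (assumed) | variance ratio | effective sample gain | 80% power becomes |
|---|---|---|---|
| 0.5 | 0.75 | 33% | 90% |
| 0.7 | 0.85 | 18% | 86% |
| 0.8 | 0.90 | 11% | 84% |
| 0.9 | 0.95 | 5% | 82% |

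**4. With dropout.** In 400 simulated trials per setting (64 per arm, 25% random dropout), the stated model's estimate correlated 0.98 to 0.99 with the completers' change difference. It is not identical, because participants with T0 only contribute. The SD of the estimate was 0.305 as written against 0.271 with a common T0 mean at rho 0.5, and 0.247 against 0.232 at rho 0.7.

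**5. Baseline or frailty?** Frailty x Time alone lowers the variance only if mean change differs between strata, by D seconds say. With a pre-frail share of 49/121 = 0.405 and a pooled variance of 0.405 × 3.15² + 0.595 × 0.98² ≈ 4.58, unadjusted over adjusted variance is 1 + 0.405 × 0.595 × D²/4.58. That is 1.01, 1.05 and 1.21 for D = 0.5, 1 and 2 s.

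A simulation of power gives the same picture (3000 trials; 36 pre-frail and 54 robust completers; lognormal TUG with means 12 and 9 s and the implied SDs; an assumed 8% benefit):

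| Model | rho 0.6 | rho 0.75 |
|---|---|---|
| as written | 53.6% | 74.5% |
| plus Frailty x Time | 53.7% | 74.8% |
| baseline adjustment only | 62.9% | 80.3% |
| baseline and frailty | 65.7% | 81.8% |

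**6. At the plan's own effects.** Pooled difference: 0.405 × 3.22 + 0.595 × 0.82 = 1.79 s. Pooled SD: √4.58 = 2.14 s, taken as the SD of the analysed quantity. Completers per arm: 128 × 0.75/2 = 48. The standardised difference is (1.79/2.14) × √24 = 4.10, so power is Φ(4.10 − 1.96) = 98%. The simulation with the plan's differences gave 98.9% as written and 99.8% with baseline and frailty at rho 0.6.

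**7. If the pooled effect were 1.0 s.** (1.0/2.14) × √24 = 2.29, so power is Φ(0.33) = 63% as written. Dividing 2.29 by √0.75 or √0.85 gives 75% (rho 0.5) or 70% (rho 0.7).

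**The case against.** The strongest reply is that nothing here is invalid. The difference in change is unbiased under randomisation, and leaving out a stratifier tends to make the standard error conservative. On the planning effects the pooled test is already close to certain to succeed. Frailty is not ignored either, since the model is rerun within each stratum and the trial was sized on those comparisons. A fuller analysis plan might add covariates. All of this stands except the last as a defence: the article gives a definite list of fixed effects and does not say that others will follow.

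Some stronger readings are tempting, and the documents do not support them:

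- **Chance imbalance in frailty or site distorts the result.** The interaction is a within-person contrast, so stable level differences between strata or sites cancel. Only imbalance in something that predicts change would remain, and frailty is balanced by the separate schedules.
- **Omitting site is an error.** Recruitment is "64 in Switzerland, 32 in Canada and 32 in Belgium", but site is not a named stratifier, and nothing in the documents quantifies a gain from adding it.
- **The model assumes one variance for both strata.** The implied SDs are about threefold apart, but the article does not state the covariance or residual structure.
- **TUG should be analysed on the log scale.** The sample-size section does say "As data might not be normally distributed, a non-parametric test was required". A log analysis, however, replaces a difference in seconds, the scale on which the trial is sized, with a ratio. A simulated advantage from lognormal data with a proportional effect follows from those assumptions.

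**Conclusion.** The point holds as one of efficiency. The stated primary model is, exactly or very nearly, an unadjusted change-score comparison. A baseline-adjusted analysis of the same data would have 5% to 25% less variance for rho between 0.9 and 0.5. The algebra is firm given equal variances at the two visits; the size is not, because the documents give neither rho nor the SDs.

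Baseline supplies most of the gain. The reason to include frailty is mainly consistency with the randomisation: it added 1.5 to 2.8 points of simulated power on top of baseline, and at most 0.3 points without it.

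A reader might infer that the trial is underpowered or its primary result unreliable. Neither follows. Pooled power at the planning effects is about 98–99% as written. The improvement would show mainly if the true effect is smaller, for example 63% against 70–75% at 1.0 s.

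**What to change.** Restate the primary model as Time, Intervention x Time, Frailty and Frailty x Time, with no Intervention main effect, so that both arms share one T0 mean within each frailty stratum. Intervention x Time remains the treatment effect. Alternatively, use ANCOVA of T1 on T0 with intervention and frailty as terms. If the mixed model is kept, Frailty must be crossed with Time, since a main effect alone leaves the estimate of change as it was. Use the same model for the continuous secondary outcomes. In the separate robust and pre-frail analyses keep the common T0 mean and drop the frailty terms. Site with Site x Time may be added as an option.

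The cost is a change of wording and a few degrees of freedom, with no new data and no change to the estimand in seconds. It should be fixed before treatment codes are revealed to the analysts. The ANCOVA version uses only participants with a T1 value, whereas the constrained mixed model also keeps those with T0 only, in line with the plan to include all participants.

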## Objectives and hypotheses

The StayFitLonger study has two major objectives that will be addressed in the trial and the sub study. The **efficacy trial** will test the effect of the training on physical, cognitive, affective, and psychosocial outcomes using a 26-week double-blind parallel-group randomised control trial (RCT). Participants will be allocated randomly to either the StayFitLonger training home-based computerised programme (experimental intervention) or a home-based computerised comparator (active control). The primary objective is to assess whether the StayFitLonger programme leads to larger pre-post improvement than the active control condition on the Timed-Up & Go (TUG), a broadly used and validated functional physical task to measure lower extremity function, mobility and balance. Participants allocated to the experimental intervention are expected to show larger post-training improvement on the TUG than participants in the control intervention. As a secondary objective, we will assess whether the StayFitLonger programme improves physical, cognitive, affective, and psychosocial secondary outcomes. We will also explore whether gains differs in robust vs. pre-frail seniors since some studies suggest that changes in response to training might depend on frailty status [11, 14].

The **adherence sub-study** will rely on a pragmatic quasi-experimental design. At the end of the 26-week RCT, participants in the experimental group will be asked to continue using the programme and participants in the control group will ‘cross-over’ to the StayFitLonger programme. This sub-study will last 22 weeks and indicators of adherence will be recorded throughout the entire duration of the StayFitLonger study (48 weeks). This will allow us to assess whether adherence is maintained over time and whether it is influenced by personal characteristics, the presence or not of supervision and the type of intervention. Usability, acceptability and user experience will also be evaluated.

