##### Analysis of moderators

Age, sex, education and score on MoCA, four variables considered as time-invariant for the duration of the study, will be assessed as potential moderators of the impact of training on primary and secondary outcomes. Prior to their use, we will verify that they are independent from each other with a chi-squared test or correlations.

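### The plan asks whether gains differ by frailty status but fits only separate models in robust and pre-frail participants, and plans no comparison between the two strata

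*Protocol article*

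**What the plan says.** The protocol article, under Objectives and hypotheses, sets the question: "We will also explore whether gains differs in robust vs. pre-frail seniors".

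The section on analysis of efficacy describes a linear mixed model for the whole sample: "The fixed effects will be Intervention (StayFitLonger vs. active control), Time (T0, T1) and their interaction". All tests are two-tailed at .05. For frailty, the same section says that "participants will be stratified into robust and pre-frail seniors and data will be analyzed separately in these two populations", by the same method.

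Under Analysis of moderators the list is "Age, sex, education and score on MoCA, four variables considered as time-invariant for the duration of the study". The abstract adds expectation and adherence. Frailty status is in neither list.

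The sample size section says "we determined our sample size to ensure that we have the capacity to test the hypotheses related to this stratification" and names the plan as "marker-by-treatment interaction using separate test". It then gives two calculations, each comparing the two arms within one stratum. For pre-frail participants, "16 participants per group (StayFitLonger vs. active control) would be required to detect a significant difference of 3.22 s in the TUG test", with no power stated. For robust participants, 23.5 per group for 0.82 s, "using a two-sided t-test (alpha = 0.05) with a power of 80"%.

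**The concern.** Whether gains differ by frailty is a question about one quantity: the treatment effect in pre-frail participants minus the treatment effect in robust participants. The described analysis produces two treatment effects and two significance verdicts, but no estimate or test of that quantity. A significant result in one stratum and a non-significant one in the other is not evidence that the effects differ, least of all when the strata differ greatly in precision, as the planning figures here imply.

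The Discussion section says both groups are included to judge the programme's relevance across physical capabilities, and that difficulty could be adjusted for future use. A spurious finding that the programme works in robust but not in pre-frail seniors (or the reverse) could feed into that decision.

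The sample size wording adds to the risk. A reader could take it to mean that the trial was sized to detect a frailty interaction, and no such calculation is shown.

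**Working it through.** **Inputs from the sample size section.** Pre-frail: 16 per group, 3.22 s, power not stated. Robust: 23.5 per group, 0.82 s, 80% power. Two-sided alpha 0.05. Non-parametric allowance from 16 to about 18 per group. Dropout about 25%. Enrolment 24.5 and 36 per group; total 122.

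**Reproducing the plan's figure.** An inflation factor of 1.15, followed by division by 0.75, recovers it:
- Pre-frail: 16 × 1.15 / 0.75 = 24.5 per group.
- Robust: 23.5 × 1.15 / 0.75 = 36.0 per group.
- Total: 2 × (24.5 + 36) = 121, or 122 with 24.5 rounded up to 25.

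The total is thus the sum of two within-stratum sizes. No between-stratum contrast enters it.

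**Implied SDs (assumption).** No SD is given, so I solved the two-sample t-test power equation (noncentral t) for it:
- Pre-frail at an assumed 80% power: standardised effect 1.024, SD = 3.22 / 1.024 = 3.15 s. At 90% power: 1.185, SD = 2.72 s.
- Robust at 80%: standardised effect 0.835, SD = 0.82 / 0.835 = 0.98 s.

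**Planned completers per group.** Pre-frail 24.5 × 0.75 = 18.4; robust 36 × 0.75 = 27.

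**Same true effect of 0.82 s in both strata.** P(significant in robust only) = robust power × (1 − pre-frail power).

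| Setting | Robust power | Pre-frail power | Robust only |
|---|---|---|---|
| Completers, SD 3.15 | 0.854 | 0.120 | 0.75 |
| Completers, SD 2.72 | 0.854 | 0.144 | 0.73 |
| 16 and 23.5 per group, SD 3.15 | 0.800 | 0.110 | 0.71 |
| 16 and 23.5 per group, SD 2.72 | 0.800 | 0.131 | 0.70 |

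The last two rows treat the non-parametric allowance as fully used up.

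**Other shared effects.** P(exactly one stratum significant) = p1(1 − p2) + p2(1 − p1), at completers with SD 3.15:

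| Shared effect (s) | Exactly one significant |
|---|---|
| 0 | 9.5% |
| 0.25 | 19% |
| 0.5 | 46% |
| 0.82 | 77% |
| 1.0 | 82% |
| 2.0 | 53% |
| 2.5 | 35% |
| 3.22 | 15% (6% with SD 2.72) |

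It exceeds one half only for shared effects of about 0.54 to 2.09 s (upper end 1.81 s with SD 2.72). If the strata instead share a standardised effect, it peaks at about 51%.

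**Power of a direct contrast under the plan's own effects.** The difference is 3.22 − 0.82 = 2.40 s.
- SD 3.15: SE = √(2 × 3.15²/18.4 + 2 × 0.98²/27) = 1.07; 2.40/1.07 = 2.24; power about 61%. Difference detectable with 80% power: about 3.0 s.
- SD 2.72: SE = 0.94; 2.40/0.94 = 2.56; power about 73%. Detectable difference: about 2.6 s.

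At 16 and 23.5 per group the same calculation gives 55% and 67%.

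**Variance assumption in a pooled model.** The noisier stratum is also the smaller one, so a single common residual variance understates the SE of the contrast. With 18 and 27 per arm and the SDs above, simulation under equal effects rejects in about 10% of trials (10.1% with SD 3.15, 9.7% with SD 2.72). With stratum-specific variances the rate is 5.0%.

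**The case against.** Much of the opposing case stands. The aim is worded as exploratory, and the sample size section calls the stratified analyses secondary. The design label does say that separate tests are used, and sizing each stratum for its own efficacy question is coherent. The two stratum estimates are essentially independent, so anyone could derive their difference and CI from the planned output. Separate models also let each stratum keep its own variance.

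A reader might infer that the plan will usually show a false frailty difference. The documents do not support that: it holds only for shared effects in the middle range above, and 0.82 s in both strata is not the plan's own scenario, which assumes 3.22 s in pre-frail participants. Nor does any section say that significance in one stratum alone will be read as a difference.

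A reader might also count the overall and two stratum tests together as inflated error on the primary outcome. That is a separate matter, and nothing in the document lets a stratum result count as trial success.

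The power figures rest on back-solved SDs. The planned mixed model uses both T0 and T1, so its precision depends on a pre-post correlation that is not given.

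None of this supplies the missing comparison. The article does specify the frailty analysis, so this is not a detail left to an analysis plan, and what it specifies does not estimate the quantity asked about.

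**Conclusion.** The point holds in limited form. The plan states a between-stratum question, describes only within-stratum analyses, leaves frailty out of the moderators, and sizes only within-stratum comparisons under a label that mentions interaction.

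If the true benefit were 0.82 s in both strata, about 70 to 75% of trials would be significant in robust only and could suggest a difference that does not exist. This assumes the back-solved SDs and the planned stratum sizes. A direct contrast would have about 61 to 73% power for the plan's own 2.40 s difference, the range reflecting the unstated pre-frail power.

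Severity is should-fix: the objective is exploratory or secondary, and the whole-sample primary comparison is untouched.

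**What to change.** In the analysis section:
- Keep the stratum-specific treatment effects and report them as estimates with CIs.
- Add the Intervention × Time × Frailty contrast, that is, the difference in treatment effect between strata, with its 95% CI. Allow different variances in the two strata.
- State that this contrast is the only basis for saying that gains differ by frailty status.

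In the sample size section, say that the trial is sized for within-stratum comparisons. Add that interaction power under the planning effects is about 61 to 73%, and that this depends on the unstated pre-frail power and on back-solved SDs. If the authors hold the actual SDs and pre-frail power, they should state them and replace the range.

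The cost is a few sentences and one less favourable power statement. No new data or change to recruitment is needed. Limited power for the contrast is a reason to report its interval, not to rely on separate significance verdicts.
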